### Data collection and analysis

2.14

The information will be collected through primary sources of information, that is, structured odontograms for research. The data will be stored in an Excel database, where the cells will be censored to reduce errors during data capture. For the analysis, the database will be exported to Stata 14.0, where a univariate analysis will be carried out first and followed by a bivariate analysis to find associations between the dependent and independent variables. Non-parametric statistical tests will be used due to the variables’ measurement scale.

#### Collection and analysis of the data regarding caries incidence

2.14.1

The incidence of dental caries will be analyzed using the ICDAS at 6, 12, 18, and 24 months after the intervention. The data will be collected by a researcher trained in this measurement system.^[34,35]^ The collected data will be captured according to the codes established in the ICDAS manual.

Caries status

0 = Sound

1 = First visual change in enamel (whitespot seen after 5 s air drying).

2 = Distinct visual change in enamel (whitespot seen without air drying).

3 = Localized enamel breakdown due to caries with no visible dentin

4 = Non-cavitated surface with underlying dark shadow from dentin

5 = Distinct cavity with visible dentin

6 = Extensive distinct cavity with visible dentin. An extensive cavity involves at least half of a tooth surface and possibly reaching the pulp.

7 = Tooth extracted because of caries (tooth surfaces will be coded 97)

8 = Tooth extracted for reasons other than caries (tooth surfaces will be coded 98)

9 = Unerupted (tooth surfaces coded 99)

In each of the measurements, the change occurred in the occlusal surfaces of the first permanent molars between the two preventive treatments used to determine which is more effective in preventing caries in each of the established periods.

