### Study design

2.1

This is a randomized experimental design that will be carried out on the FPMs of schoolchildren from public elementary schools in the state of Hidalgo, Mexico. Start date: 2019–03-05.

Hidalgo is one of the 31 states, which, with Mexico City, comprise the 32 Federal Entities of Mexico. It is divided in 84 municipalities and its capital city is *Pachuca de Soto*. Hidalgo is one of the Mexican states that participated in the fluoridated domestic salt program implemented nationally in 1991. Mexico has no water fluoridation program at the national level; however, some states, including parts of Hidalgo, have water with naturally high levels of fluoride. This is not the case in Pachuca, the capital city of Hidalgo.^[27,28]^

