### Inclusion criteria

2.4

Children must be from 6 to 8 years of age, belong to the selected public elementary schools, and:

Have at least one first molar that is healthy and fully erupted;Whose parents sign the informed consent form; andDecide to participate in the intervention.

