### Trial intervention

2.6

The PFSs to be used in this study have been used for years in other populations. Children will be randomly assigned to either the PFS or varnish group and each subject will remain in their assigned group throughout the study.

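### Children are randomised and counted, but caries is compared on first-molar surfaces with bivariate tests, and no step allows for several molars in one child

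*Protocol article*

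**What the plan says.** - **Randomisation is by child.** Section 2.6: "Children will be randomly assigned to either the PFS or varnish group and each subject will remain in their assigned group throughout the study". All eligible molars in a mouth therefore belong to the same arm.
- **The sample size is by child.** Section 2.10 uses a difference of proportions (60% and 40%) with 80% power, giving 97 subjects, raised to 114 per group for losses.
- **A child may bring more than one molar.** The tooth-related entry condition in section 2.4 is a minimum: "Have at least one first molar that is healthy and fully erupted". Section 2.1 places the trial on the first permanent molars: "This is a randomized experimental design that will be carried out on the FPMs of schoolchildren from public elementary schools".
- **The outcome is described on surfaces.** Section 2.8 defines incidence as visible change in the enamel surface against baseline, at 6, 12, 18 and 24 months. Section 2.14.1 gives the comparison at each visit as "the change occurred in the occlusal surfaces of the first permanent molars between the two preventive treatments used".
- **The methods are simple two-variable tests.** Section 2.14: "a univariate analysis will be carried out first and followed by a bivariate analysis to find associations between the dependent and independent variables", and "Non-parametric statistical tests will be used due to the variables’ measurement scale".

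**The concern.** Two parts of the plan do not fit together. Allocation and sample size treat the child as the unit, while the described comparison is of molar surfaces. Molars in one mouth share diet, hygiene and caries risk, so their results can be expected to be positively correlated. Because they also share the treatment, that correlation adds directly to the variance of the difference between arms.

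The usual two-group non-parametric tests assume independent observations. The reason the article gives for choosing them is measurement scale, which does not address dependence. An analyst who followed sections 2.14 and 2.14.1 literally could enter every molar as a separate observation. The standard errors would then be too small, and a difference between sealant and varnish would be declared too often at each of the four time points. Any interval attached to the effect used for cost-effectiveness would also be too narrow.

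**Working it through.** **1. The plan's own figure.** Inputs from section 2.10: proportions 0.60 and 0.40, power 80%. The stated α of 95% is read as 95% confidence, so alpha is 0.05, and a two-sided test is assumed. With pooled variance and no continuity correction:

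n = [1.96·√(2·0.5·0.5) + 0.8416·√(0.6·0.4 + 0.4·0.6)]² / (0.6 − 0.4)²
= (1.386 + 0.583)² / 0.04 = 96.9, so 97 per group.

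This matches the plan. For losses, 97 / (1 − 0.15) = 114.1, which agrees with 114. The calculation takes one binary result per child. If 60% and 40% apply per child, power is 80.0% at 97 per group and 86.0% at 114.

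**2. What changes if molars are the rows.** Let m be the number of molars per child and ICC the within-child correlation.

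- Design effect: DE = 1 + (m − 1)·ICC
- Naive SE divided by correct SE: 1/√DE
- Real type I error of a nominal two-sided 5% test: 2·[1 − Φ(1.96/√DE)]

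The minimum of one molar is in section 2.4, and the maximum of four is anatomy. The mean number is not given, so 2, 3 and 4 are shown. The ICC is not given either; 0.1 to 0.5 is an assumption.

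Example with m = 2 and ICC = 0.3: DE = 1.3, √DE = 1.140, 1.96/1.140 = 1.719, type I error 8.6%.

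| Molars per child | ICC | DE | Naive SE / correct SE | Real type I error |
|---|---|---|---|---|
| 2 | 0.1 | 1.1 | 0.953 | 6.2% |
| 2 | 0.3 | 1.3 | 0.877 | 8.6% |
| 2 | 0.5 | 1.5 | 0.816 | 11.0% |
| 3 | 0.1 | 1.2 | 0.913 | 7.4% |
| 3 | 0.3 | 1.6 | 0.791 | 12.1% |
| 3 | 0.5 | 2.0 | 0.707 | 16.6% |
| 4 | 0.1 | 1.3 | 0.877 | 8.6% |
| 4 | 0.3 | 1.9 | 0.725 | 15.5% |
| 4 | 0.5 | 2.5 | 0.632 | 21.5% |

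**3. Check by simulation.** Beta-binomial data with 97 children per arm, 50% incidence and 20,000 runs gave, for ICC 0.1, 0.3 and 0.5:

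- two molars: 5.7%, 8.2%, 10.4%
- four molars: 8.1%, 15.3%, 21.0%
- one to four molars in equal shares: 7.5%, 12.4%, 16.7%

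Where both exist, formula and simulation agree within about 0.6 percentage points.

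**4. Effective sample.** With two molars, 97 children give 194 molars, worth 194/1.1 = 176 independent molars at ICC 0.1 and 194/1.5 = 129 at ICC 0.5. With four molars, 388 are worth 388/1.3 = 298 and 388/2.5 = 155. The loss therefore ranges from slight to severe.

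**The case against.** The strongest reply is that the unit of analysis is inferred. The key sentence in section 2.14.1 is grammatically incomplete. It says where change is recorded, not what forms a row in the test. Any new lesion, the worst ICDAS code or a lesion count per child would each also be a change on those surfaces. A chi-square or Mann-Whitney test on one such value per child is bivariate, non-parametric and valid. The sample size in subjects, and the primary result in section 2.8 stated between groups, fit that reading. A condensed article may also leave the choice of model to a fuller document.

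Much of this stands. A reader might infer that the plan commits to testing molars as independent; the text does not go that far, so the inflation is conditional. A reader might also take the four-molar figures as typical. They are the upper end: one sound, fully erupted molar is enough to enter at age 6 to 8, and the coding list in section 2.14.1 includes unerupted teeth.

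What does not stand is that this is only omitted detail. The article states an outcome level and a test family and gives a reason for the tests. Taken together as written, these lead naturally to an analysis that ignores clustering, and no section states a child-level result that would prevent it.

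**Conclusion.** The point holds as a mismatch that needs correcting: allocation and sample size are by child, the described comparison is by surface, and the named tests make no allowance for several molars in one child. If molars are tested as independent, the naive standard error is about 5% to 37% too small (ratios 0.953 to 0.632), and false positives occur at roughly 6% to 21% instead of 5%. The direction follows for any positive within-child correlation with more than one molar per child. The size rests on an assumed correlation of 0.1 to 0.5 and on two to four molars per child.

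Two further inferences are not supported. The sample size is not wrong on this ground: it is already per child, and additional molars add information rather than raise the number of children needed. The point estimate entering the cost-effectiveness ratio is not biased merely because clustering is ignored; only its precision would be overstated, and section 2.14.2 mentions no interval for the ratio.

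**What to change.** In sections 2.14 and 2.14.1, state that the child is the unit of inference, and adopt one of two routes for the primary comparison:

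1. **Molar level.** Analyse new caries on each eligible first molar with a binomial GEE, or with regression using cluster-robust variance, clustered on the child. Report a risk difference with its 95% CI at each visit. Both methods are available in Stata 14, the software already chosen.
2. **Child level.** Define one primary outcome per child: any new lesion on a first molar that was sound at baseline. The bivariate tests already named are then valid, and the outcome matches the 97/114 calculation. Because a child with more molars at risk has more chances of a lesion, add an analysis adjusted for that number.

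Whichever is chosen as primary, the other can serve as a check. The cost is a few sentences of analysis text and at most one model, with no change to recruitment, treatment or data collection. Confidence intervals will be somewhat wider than a naive molar-level analysis would give, and the child-level route gives up information on how many molars were affected.

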#### Analysis of the cost of the intervention

2.14.2

Once the direct cost of the interventions is obtained, the cost-effectiveness ratios will be generated as recommended in the literature.^[36]^

## Discussion

3

Dental caries is one of the most frequent problems of the oral cavity. It affects more than half of the child population worldwide and is the leading cause of tooth loss in children and young adults.^[1]^ At present, there are different preventive methods that allow practitioners reduce the incidence of caries, among which the methods used in this intervention stand out; however, in Mexico, such work is still very scarce. The design of the present study will allow us to compare the effectiveness of both technologies and determine the total cost and cost-effectiveness of each. The information generated by this work can contribute to the decision-making of health planners.

In Mexico, the use of technologies that prevent oral diseases, other than those derived from fluoride, is limited, e.g., the low rate of use of PFSs reported by the Epidemiological Surveillance System for Oral Pathologies.^[26]^

The benefit of carrying out preventive programs in children is that they improve the subjects’ quality of life, reduce the risks of general disease, and reduce future out-of-pocket expenses for the population and health systems associated with the treatment of this disease.^[28,37]^ Results will be disseminated in Mexican and international scientific and professional venues.
